### Phase I

#### Sampling

To increase the comparability of the two school groups, stratified sampling, based on propensity scores, was used.^17^ We obtained routine data from the DfE on several characteristics for all schools in the sampling frame: Local Authority area; establishment type; urban/rural; total pupil roll size; Income Deprivation Affecting Children Index; inclusion of a sixth form; selective/non-selective admissions policy; religious affiliation/secular; and proportion of: male/female pupils; pupils from Black, Asian and ethnic minority groups; students with English as a foreign language; students eligible for free school meals; and pupils with Special Educational Needs. We developed propensity scores using linear regression with the SFS status of the school (mandated/non-mandated) as the outcome and school characteristics as explanatory variables. Propensity score quartiles were then used to create four groups with subsequent division by SFS status (based on the date they received academy/free school status), resulting in eight distinct sampling groups. Following the random ordering of each group, schools will be invited sequentially to participate, aiming to recruit five or six schools from each group.

Within participating schools, pupils in one class from each of years 7, 9 and 10 (aged 11–12, 13–14 and 14–15 years, respectively) will be invited to take part. Preference will be given to classes not streamed by academic ability or subject to enable participation of classes that are representative of the year group characteristics. There are no pupil exclusion criteria.

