#### Data analysis

##### Preliminary development of a school typology

Using the logic model (figure 1) as a guide, we will use data captured on SFS/SFP implementation and the school context to develop an initial typology of schools, which will reflect the degree of implementation of the SFS/SFP and other relevant local initiatives relating to food and healthy eating.

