##### Analysis of pupil outcomes

Pupils will have a maximum of two 24-hour recalls for dietary intake measures. To summarise dietary outcomes, we will report the average value across the 2 days for each pupil. If only a single day is available, we will use data from that day only. Differences between the SFS mandated and SFS non-mandated school groups for both primary and secondary pupil outcomes will be assessed using multilevel linear models that account for clustering at the school and class level (and at the Multi-Academy Trust level if applicable). Models will include adjustment for propensity scores and pupil-level covariates (school year group, sex, ethnicity, IMD score and school-provided vs home-packed lunch). Models for dietary outcomes will use data recorded each day, allowing for the repeated outcome measures. Models for dental outcomes will be additionally adjusted for oral healthcare factors and water fluoridation exposure. We will also explore whether the associations between school SFS status and pupil outcomes differ across age, socioeconomic position (indicated by IMD score), or usual lunch type (school-provided vs home-packed) by adding the relevant interaction terms to the developed models. If more than 5% of data are missing from demographic variables, multiple imputation methods will be used and sensitivity analyses conducted.

If possible, within the group of schools which are not mandated to adhere to the SFS, we will undertake an exploratory analysis to examine differences in pupil outcomes between schools who have and have not voluntarily signed up to the SFS. In addition, we will develop further linear multilevel models to explore potential associations between the identified school types and pupil outcomes, again adjusting for clustering, potential pupil-level confounders and propensity scores, as described previously.

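### The school-type models adjust for a propensity score built for mandate status, which does not ensure balance across school types

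*Protocol article*

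**What the plan says.** The protocol article describes one propensity score. Under Sampling: "We developed propensity scores using linear regression with the SFS status of the school (mandated/non-mandated) as the outcome and school characteristics as explanatory variables". Thirteen characteristics from routine education data are listed as available for it, among them "total pupil roll size; Income Deprivation Affecting Children Index; inclusion of a sixth form; selective/non-selective admissions policy", and the shares of pupils by sex, ethnic minority group, language, free-school-meal eligibility and special educational needs. Quartiles of the score, split by mandate status, gave the eight sampling groups.

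School type is defined elsewhere. Preliminary development of a school typology describes a classification "which will reflect the degree of implementation of the SFS/SFP and other relevant local initiatives relating to food and healthy eating". The opening of Methods and analysis adds wider contextual factors as a basis for it.

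Analysis of pupil outcomes first sets out the models for the mandate contrast, adjusted for propensity scores and for "pupil-level covariates (school year group, sex, ethnicity, IMD score and school-provided vs home-packed lunch". It then turns to school type: "we will develop further linear multilevel models to explore potential associations between the identified school types and pupil outcomes". No score for school type is named, and no school characteristic is named as a direct covariate. The adjustment given for these models is "again adjusting for clustering, potential pupil-level confounders and propensity scores, as described previously".

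**The concern.** A propensity score balances the characteristics it contains between the groups whose membership it predicts. This score predicts mandate status, which follows from the date a school gained academy or free school status. School type is a different exposure. Two schools with the same mandate score can differ in roll size, admissions policy, sixth form or share of deprived pupils. If those features go with both implementation and diet, the school-type coefficient absorbs part of their effect.

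The text gives some reason to expect such links. Assessment of school contextual factors places the socioeconomic and demographic make-up of the pupils among the contextual data, and context feeds the typology. Type and intake may then be related by construction.

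The comparison is not marginal. The abstract lists it beside the mandate comparison for diet and dental health, and the economic evaluation is to show how costs and outcomes vary by school type. Calling the estimates propensity-adjusted would invite more confidence than the adjustment earns.

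**Working it through.** **Is the mandate score really the one carried over?** The outcome of the score is mandate status (Sampling). The exposure in the later models is school type (Preliminary development of a school typology). The adjustment is the score already described (Analysis of pupil outcomes), and the article describes no other. So this is a stated rule, not a detail left open.

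**What else is in the school-type models?** Year group, sex, ethnicity, IMD score and lunch type, all at pupil level. Pupil IMD score and ethnicity take out part of any confounding by deprivation and ethnic composition. They do not directly measure roll size, selectivity, sixth form or the concentration of deprivation in a school.

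**How much bias could remain?** The plan gives no figure for this analysis, so there is none to reproduce; its sample size is set on the mandate contrast and is not used here. What follows is an illustration, and every input is an assumption:

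- C is a standardised index of school-level confounding that drives both school type and outcome.
- Type is taken as two groups split on 0.5·C + √0.75·noise, so its squared correlation with C is a² = 0.5² × 2/π = 0.159.
- r is the correlation of the mandate score with C.
- ρ is the correlation with C of what the pupil covariates capture, entered as a school-level stand-in.
- Given C, the score, the pupil covariates and type are independent.

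Let R² be the share of variance in C explained by score and pupil covariates together:

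R²/(1 − R²) = r²/(1 − r²) + ρ²/(1 − ρ²)

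Share of bias remaining = (1 − R²)/(1 − a²R²)

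Example with r = 0.5 and ρ = 0.5: R²/(1 − R²) = 0.333 + 0.333 = 0.667, so R² = 0.40, and the share remaining is 0.60/(1 − 0.159 × 0.40) = 0.60/0.936 = 0.64.

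| r | Score only (ρ = 0) | With pupil covariates, ρ = 0.5 | With pupil covariates, ρ = 0.8 |
|---|---|---|---|
| 0 | 100% | 78% | 40% |
| 0.1 | 99% | 78% | 40% |
| 0.3 | 92% | 73% | 39% |
| 0.5 | 78% | 64% | 36% |
| 0.7 | 55% | 48% | 30% |
| 0.9 | 22% | 21% | 16% |

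A simulation with 400,000 draws per setting agrees with every cell to within about one percentage point.

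The row r = 0 shows what the pupil covariates do alone: 78% remains at ρ = 0.5 and 40% at ρ = 0.8. At r = 0.3 the score lowers these only to 73% and 39%. It helps much only if it happens to track the confounders of school type closely, and nothing in its construction aims at that.

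**The case against.** The strongest objection is that the quoted sentence does more than reuse the score. It also adjusts for pupil confounders, including IMD score and ethnicity, and the score is itself built from area deprivation, roll size and intake. A reader might infer that confounding by deprivation, size and intake is left almost untouched. The document does not support that. It would need a weak link between score and confounders (r of about 0.3 or less) and pupil covariates that capture little of them, and the document fixes neither. Likewise, a range such as 60% to 95% remaining can be reached only by leaving the pupil covariates out, which is not the model in the plan. This part of the objection stands, and it limits the point to a lack of assurance.

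A reader might also extend the point to the voluntary sign-up analysis among non-mandated schools ("differences in pupil outcomes between schools who have and have not voluntarily signed up to the SFS"). The reference to the score belongs to the later sentence on school types. The sign-up sentence states no adjustment set, so reuse there would be inference.

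The school-type analysis is worded as exploring associations, with a typology still to be built, and a journal article may leave fine detail to a fuller document. That lowers the stakes. It does not remove the point, because the article states which score will be used.

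Finally, the score has a reason to stay, since its quartiles were sampling strata. And if pupil make-up helps to define the types, adjusting for it could remove part of the exposure. Both objections stand and shape the fix.

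**Conclusion.** The point holds in a limited form. The mandate score is not a balancing score for school type, so school-level confounding of the school-type associations is not reliably controlled beyond what the pupil covariates remove. The size of the residual bias cannot be derived from the document. The 16% to 100% span in the table rests on assumed correlations, a single confounding index and a two-group typology. It shows only that the remainder may be large or small.

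The mandated versus non-mandated comparison is unaffected: there the score matches the exposure. The change is worth making because the abstract gives the school-type comparison a place beside the main one and the remedy uses data already in hand.

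**What to change.** In the school-type models:

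- Keep the mandate score, or its quartile, as a sampling-design variable.
- Add a short prespecified list of the school characteristics already obtained for the sampling frame, for example area deprivation index or free-school-meal share, roll size, ethnic-minority share and selective admissions.
- Leave out of that list any characteristic used to define the types, and say which were left out.
- Do not describe the school-type estimates as propensity-adjusted on the strength of the mandate score alone.

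A separate score for school type is an alternative, but with 44 schools and an unknown number of types it may be unstable, so direct adjustment is the simpler choice.

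The cost is a change of wording and about three to four school-level degrees of freedom out of 44 schools. No new data are needed, and the models for the mandate contrast stay as they are.

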### Phase II: school case studies

A number of schools (n=4–8) will be asked to participate in a qualitative study. Schools will be selected to comprise a range of school types and include at least two schools from the SFS non-mandated group not reporting voluntary sign up. These schools will receive a further £150.

We will undertake interviews with key school stakeholders (identified by the school Senior Leadership Team, aiming for 4–6 per school) to explore in more depth the way in which the SFS/SFP and local school policy or initiatives are introduced, embedded and sustained in the schools, and their perceived influence on the dietary intake of pupils. Data collection will be shaped with reference to the four constructs, and their constituent components, within May *et al*’s NPT^25^ and by Maguire *et al*’s exploration of policy enactment in English schools.^35^ Interviewees will be encouraged to tell their ‘story’ relating to their experiences of the SFS/SFP; how the provision of food, eating environments and the food/cooking curriculum have been shaped within their schools; and the influence of the wider school context.

Through focus groups (FGs) with school pupils (aiming for one FG in each included year group per school, comprising 6–8 participants per FG) we will explore their views of the school food environment, contextual factors influencing this, and how they interact with this and the wider external environment surrounding the school, in terms of their eating behaviour. We will also explore the views and experiences of any negative impact of SFS/SFP and the regulation of foods provided. Participating pupils will receive a £5 voucher.

Interviews/FGs will be audio-recorded with participant consent, transcribed ad verbatim and anonymised. We will use the framework analytical approach,^36^ and within this undertake thematic analysis, guided by NPT and Maguire *et al*’s policy enactment exploration.^25 35^

### Economic evaluation

To evaluate the economic impact of the SFS and the wider SFP, a cost–consequence analysis will be undertaken. We will summarise costs and outcomes in the form of a balance sheet. The analysis will highlight the costs to schools and families, and offer a transparent range of outcome measures for consideration. In addition, we will conduct an exploratory cost–utility analysis. Quality-Adjusted Life Years (QALYs) will be constructed from pupil responses to CHU-9D to allow inferences to be made about QALY-differences between the two school groups offset against the cost.

### Patient and public involvement

During research plan development, the deputy headteacher member of the investigator team advised on engaging schools and pupils and access to food sales data and provided background information on school management and governance systems. In addition, we consulted with a group of parents of secondary school children and a group of secondary school pupils, a teacher and a manager of a school catering company, who advised on school, pupil and parent recruitment, data collection methods and survey content. To provide ongoing advice from a public perspective, we have convened a group of parents, teachers and secondary school governors (n=8), and two groups of secondary school pupils to consult with at key points throughout the study. To date, these groups have reviewed and piloted surveys and Intake24, and advised on developing a safeguarding policy; school, staff, pupil and parent recruitment and school retention; data collection practicalities; and the alternative activity for non-participating pupils.

## Ethics and dissemination

Full ethical approval for the study was obtained from the University of Birmingham Science, Technology, Engineering and Mathematics Ethical Review Committee on 20 August 2019 (ERN_18-1738).

### Data management and study oversight

The University of Birmingham is the Study Sponsor and data controller and assumes overall responsibility for the study. Data management and storage is compliant with the UK Data Protection Act 2018 and follows the relevant University of Birmingham policy and procedures. Anonymised data will be stored securely for a minimum of 10 years after the publication of the main study results.

An independently chaired Study Steering Committee (SSC) has been convened to provide study oversight. Membership comprises three independent academics with relevant expertise, a representative from Public Health England (PHE), a public representative and the Chief Investigator. The Committee has agreed on the current protocol and will review subsequent amendments.

### Dissemination

Study findings will be disseminated to key national agencies (eg, Department of Health and Social Care, DfE, PHE, School Food Alliance, National Association for Headteachers and the Lead Association for Caterers in Education (LACA)), local level organisations (eg, Regional School Commissioners and Local Authorities), and schools through reports, conference/meeting presentations, the educational and general press and open access publications. The public representatives on the Investigator team, SSC and other public engagement groups will advise further on dissemination plans for the study findings. A full report of the study will be published in the *NIHR Journals Library*. After the publication of the main study findings, anonymised data will be available on request from the study Chief Investigators.
